## Abstract

**Background:**

In the era of targeted therapies, the influence of aging on cancer management varies from one patient to another. Assessing individual frailty using geriatric tools has its limitations, and is not appropriate for all patients especially the youngest one. Thus, assessing the complementary value of a potential biomarker of individual aging is a promising field of investigation. The chronic myeloid leukemia model allows us to address this question with obvious advantages: longest experience in the use of tyrosine kinase inhibitors, standardization of therapeutic management and response with minimal residual disease and no effect on age-related diseases. Therefore, the aim of the BIO-TIMER study is to assess the biological age of chronic myeloid leukemia or non-malignant cells in patients treated with tyrosine kinase inhibitors and to determine its relevance, in association or not with individual frailty to optimize the personalised management of each patient.

**Methods:**

The BIO-TIMER study is a multi-center, prospective, longitudinal study aiming to evaluate the value of combining biological age determination by DNA methylation profile with individual frailty assessment to personalize the management of chronic myeloid leukemia patients treated with tyrosine kinase inhibitors. Blood samples will be collected at diagnosis, 3 months and 12 months after treatment initiation. Individual frailty and quality of life will be assess at diagnosis, 6 months after treatment initiation, and then annually for 3 years. Tolerance to tyrosine kinase inhibitors will also be assessed during the 3-year follow-up. The study plans to recruit 321 patients and recruitment started in November 2023.

**Discussion:**

The assessment of individual frailty should make it possible to personalize the treatment and care of patients. The BIO-TIMER study will provide new data on the role of aging in the management of chronic myeloid leukemia patients treated with tyrosine kinase inhibitors, which could influence clinical decision-making.

**Trial registration:**

ClinicalTrials.gov, ID NCT06130787; registered on November 14, 2023.

## Background

Chronological age is a limiting factor in the administration of anti-cancer treatments, but the development of targeted therapies and advances in overall management have made it possible to extend the age limit for prescribing them. The evolution of personalised medicine partly explains the reduction in mortality rates since the end of the 1990s. However, therapeutic efficacy and side effects vary from one patient to another, depending not only on age but also on the patient’s general condition and comorbidities. A better characterisation of individual biomarker for ageing is a key challenge for personalised medicine.

Ageing is classically determined by chronological age, which only partially reflects physiological ageing. The only tools used in practice to assess the individual impact of ageing are based on surveys to detect frailty [1] by assessing the functional impact of age (quality of life, cognitive capacity, mobility, autonomy), mainly developed and used by geriatricians [2]. Age-related individual frailty has been shown to influence cancer management and progression [3]. However, in the era of targeted therapies, these tools are not suitable for all patients, as most of them were developed with elderly populations [1–5]. Furthermore, they are only suitable for individual frailty that has already present but not for early frailty or the risk of developing frailty in a pathological context such as cancer.

Complementary tools to assess individual biological and functional ageing would appear to be of particular relevance [5]. The relationship between chronological age (in years) and biological age (BA) (the ageing of cells/tissues) and their relationship with the development or the treatment of cancer remains poorly defined, especially for targeted therapies. Cellular ageing is a complex and multifactorial process [5, 6] related to pathologies (Parkinson’s disease, cardiovascular disease, cancer, etc.).

Recently, biomarkers of ageing called epigenetic clock have been described. These clocks are based on DNA methylation (DNAm) and enabled an accurate estimation of BA for any tissue. In fact, changes in DNA methylation during ageing [7–10] are correlated with the risk of developing age-related pathologies and mortality. In many cancers, the DNAm clock is altered, usually towards accelerated ageing. Moreover, an association between accelerated BA and the risk of cancer has been described [9, 11], but the relationship between biological ageing and the characteristics of the cancer and/or its evolution during treatment or tolerance to treatment remains poorly understood.

Chronic myeloid leukemia (CML) appears as a model to study these relationship. Firstly, it is a model of personalised medicine with the first targeted therapy (tyrosine kinase inhibitors), and thus has the longest track record of use. Moreover, the management of CML and the assessment of therapeutic response are standardized [12]. Unlike other cancers, CML is considered to have a minor influence on the biological functions altered by ageing, thus avoiding a major confounding factor [13]. Furthermore, there is no clear relationship between CML development and predisposition factor such as clonal hematopoiesis of undetermined significance (CHIP) in the course of ageing. Finally, some preliminary results suggest the existence of age-related DNA methylation abnormalities common to all patients, regardless of age. This could be linked to the emergence and amplification of the CML clone and possibly to an individual predisposition [14]. Lastly, some tyrosine kinase inhibitors (TKI) as nilotinib and ponatinib can induce side effects considered as aging-related diseases, for example cardio-vascular toxicity. These properties make CML as a particularly suitable model for studying the influence of age-related biological features other than CHIP.

Few studies have analysed the relationship between the DNA methylation profile and individual frailty in cancer patients treated with targeted therapy. Its influence on response and, in particular, tolerance to treatment remains to be studied. In fact, the influence of chronological age is tending to decrease due to the greater efficacy and better tolerance of targeted therapies, but some patients present significant side effects that may be related to ageing.

The aim of the BIO-TIMER protocol is therefore to assess the value of combining the determination of BA using the DNA methylation clock with the assessment of individual frailty in order to personalise the management of CML patients treated with TKI.

## Methods and analysis

### Study design

The BIO-TIMER study is a multi-center, prospective, longitudinal study aiming to evaluate the value of combining BA determination with individual frailty assessment to personalize the management of CML patients treated with TKI. This study has been registered on Clinicaltrials.gov (NCT06130787). A maximum of 321 patients are expected to be enrolled. The study was started in November 2023 with a 2-year enrolment period and an estimated completion date by November 2028.

### Coordination and participating institutions

The CHU Clermont-Ferrand is the sponsor and is responsible for coordination, trial management, data management, trial monitoring and statistical analysis. This multicenter study will be conducted in 16 sites in France. The list of the study sites is available on https://clinicaltrials.gov/study/NCT06130787.

The CRB-Auvergne (BB-0033-00039) coordinates the collection of biological samples. All activities have been certified according to the NF S 96–900 standard since July 2013, ISO 9001 certified since July 2020 and ISO 20,387 certified since October 2022 thus ensuring the quality of biological resources, harmonization of professional practices and compliance with current regulations.

### CML observatory

The clinico-biological data from patient follow-up will be recorded in an already existing database: the CML observatory. The aim of the CML observatory is to establish the largest possible real-life cohort collecting long-term follow-up of a maximum number of CML patients in France, in order to carry out observational studies [15]. Any patient with a recent or previous diagnosis of CML may be included. Each patient’s clinical and laboratory data are recorded after obtaining informed consent from the patient. The record sheet has been adapted to the follow-up of patients with CML. Data recording is retrospective and prospective. In the case of the BIO-TIMER study, the data will be collected prospectively. The patient’s characteristics, treatments (dosage, treatment changes and their reasons), and laboratory results (particularly BCR::ABL transcript quantification) will be recorded. Some variables, such as prognostic scores are calculated automatically.

### Study objectives and endpoints

#### Main objective and endpoint

The main objective of the study is to evaluate the value of combining BA determination with individual fragility assessment to personalize the management of CML patients treated with TKI, in terms of tolerances.

The first primary endpoint is the difference between BA and chronological age (of the CML clone and non-malignant cells in the same patient) expressed as a difference and as a percentage (ratio).

The second endpoint is the individual frailty assessed using G-CODE score, Rockwood Frailty Scale and Charlson Comorbidity Index.

And the last endpoint is the TKI tolerance in patients with CML assessed by actual dose received, TKI discontinuation due to intolerance, TKI discontinuation due to adverse events, TKI changes due to intolerance and number of TKI lines.

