### Participant eligibility

The inclusion and non-inclusion criteria are presented in Table 1. Newly diagnosed chronic phase - CML patients will be eligible for the protocol.

**Table 1 Tab1:** Section criteria

Inclusion criteria	Non-inclusion criteria
Female or male 18 years of age or older	CML in accelerated or blast phase
CML-CP diagnosis (chronic phase) with confirmation of a Philadelphia chromosome (Ph1) made no more than 3 months (90 days) prior to inclusion. A cryptic Ph1 chromosome must be confirmed by FISH. Criteria must meet the CML chronic phase definition criteria: - < 15% blasts in peripheral blood and bone marrow - < 30% blasts + promyelocytes in peripheral blood and bone marrow - < 20% basophils in peripheral blood, - Platelet count ≥ 100 × 109/L (≥ 100,000/mm3)	
BCR ::ABL1 transcript quantifiable by quantitative RT-qPCR	Refusal to participate
1st-line treatment with tyrosine kinase inhibitors	
No treatment with tyrosine kinase inhibitors or hydroxyurea prior to first blood sampling (at diagnosis)	Treatment started before inclusion
Signature of informed consent for the CML Observatory and signature of informed consent for the BIO-TIMER protocol	Patients under guardianship, curatorship, deprivation of liberty or safeguard of justice
Read and understand French	Pregnant or breastfeeding woman
Persons affiliated to a social security system	

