### Intervention

Eligible patients will be enrolled following a consultation with an investigator, after checking that they meet the inclusion and exclusion criteria (and signing an informed consent).

The specific needs of the study are to provide a biological sample and to assess individual frailty and quality of life longitudinally.

Blood samples will be collected at diagnosis, 3 months and 12 months after treatment initiation. Optionally, a bone marrow sample taken at diagnosis will be retained. This will be used to compare the BA between the blood and bone marrow compartments.

An assessment of individual frailty and quality of life will be performed at diagnosis, 6 months after treatment initiation, and then annually for 3 years.

Pseudonymized blood samples will be stored by every sites and then sent to the CRB-Auvergne (France) for analysis. Blood samples will be analyzed to assess BA.

The risks or constraints for subjects participating in the study appear to be minimal, as the only intervention is blood tests.

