### Determination of biological age and evaluation of individual frailty

DNA methylation profile analysis is currently the most robust method for assessing BA. DNA methylation clocks mainly use data from HM450K chips (Illumina), which cover the majority of CpG islands. However, these have been replaced by the recently validated EPIC BeadChip kit, despite the loss of some targets [16]. Based on the results obtained with the EPIC BeadChip kit, BA will be determined using the Horvath [10], Hannum [7] and DNAmPhenoAge [8] algorithms, which combine the methylation profile and certain biological assays. In addition, next generation sequencing will be performed to assess the presence of mutations of CHIP and measurement of telomere length will be carried out.

These analyses will be carried out at the time of diagnosis, prior to any treatment, in order to characterise the DNA methylation profile of malignant cells. They will also be carried out 3 months and 12 months after the start of treatment, when the residual BCR::ABL1/ABL1 transcript is low. This will enable the DNA methylation profile of non-malignant cells to be described.

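### Cell type is assigned by sampling time with no stated handling of leukocyte mix, so differences in BA minus chronological age may partly reflect cell composition

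*Protocol article*

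**What the plan says.** All references are to the protocol article.

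- **Main objective and endpoint.** The first primary endpoint is BA set against chronological age, as a difference and as a ratio, "of the CML clone and non-malignant cells in the same patient".
- **Intervention.** The material is blood: "Blood samples will be collected at diagnosis, 3 months and 12 months after treatment initiation". Then: "Blood samples will be analyzed to assess BA". Marrow is optional and taken only at diagnosis, to compare BA between the two compartments.
- **Determination of biological age and evaluation of individual frailty.** Methylation is measured "at the time of diagnosis, prior to any treatment, in order to characterise the DNA methylation profile of malignant cells". Of the later samples it says: "They will also be carried out 3 months and 12 months after the start of treatment, when the residual BCR::ABL1/ABL1 transcript is low". The inference follows: "This will enable the DNA methylation profile of non-malignant cells to be described". The section names the array, three clocks, sequencing for clonal hematopoiesis and telomere length. It mentions no cell sorting, cell-fraction estimate, composition-adjusted clock or transcript threshold.
- **Participant eligibility, Table 1.** Chronic phase is defined by upper limits: below 15% blasts, "< 30% blasts + promyelocytes in peripheral blood and bone marrow", and below 20% basophils in peripheral blood.
- **Study procedures, Table 2.** The listed laboratory tests include hemoglobin but no leukocyte differential.
- **Data analysis.** Confounders are chosen from univariate results and clinical relevance. Leukocytosis appears among the example confounders given after the tolerance and response models.

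**The concern.** A methylation clock applied to whole blood gives a reading averaged over whatever cells are in the tube. Between the diagnosis sample and the on-treatment samples, at least two things change: the clone shrinks, and the proportions of the leukocyte types move towards a normal blood picture. The plan labels the first sample malignant and the later ones non-malignant, so it attributes the whole change in reading to the first process. If the clocks read leukocyte types differently, part of that change comes from the second.

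This is not the same as residual clone at 3 or 12 months. It would remain in a patient whose transcript had become undetectable.

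There is also a between-patient side. At diagnosis, patients differ in how abnormal their blood is. Some of the spread in diagnosis BA may then track disease burden, and that BA enters the frailty, tolerance and response analyses.

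**Working it through.** There is no figure in the plan to reproduce on this point. The check is a reading of the sections together, followed by an illustration on assumed inputs.

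**Step 1: what distinguishes the two cell types.** The endpoint needs a value for the clone and a value for non-malignant cells. Intervention supplies one material, blood, at three times. The biological-age section links malignant to the untreated sample and non-malignant to months 3 and 12. Sampling time is the only distinguishing feature stated.

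**Step 2: whether the mix can differ.** The Table 1 limits allow blasts plus promyelocytes anywhere from 0 to just under 30%, and basophils in blood from 0 to just under 20%. Together these cells may make up from 0 to just under 30 + 20 = 50% of leukocytes. These are ceilings, not expected values, but they leave room for large differences between patients and between visits.

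**Step 3: whether a written covariate captures the mix.** Leukocytosis is a count of all leukocytes. Two patients with the same count can have very different mixes. It is also named for the tolerance and response models, not for the BA analyses. The general confounder rule could admit a composition term but does not commit to one.

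**Step 4: how large the effect could be.** None of these inputs is in the documents. Assumed: a shift *s* in the fraction of one cell group of 0.1 to 0.4; a clock offset *o* between cell groups of 0 to 10 years; an SD of the paired BA change of 4 to 8 years.

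Spurious mean change *b* = *s* × *o*, in years:

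| s | o = 0 | o = 2 | o = 5 | o = 10 |
|---|---|---|---|---|
| 0.1 | 0 | 0.2 | 0.5 | 1.0 |
| 0.2 | 0 | 0.4 | 1.0 | 2.0 |
| 0.3 | 0 | 0.6 | 1.5 | 3.0 |
| 0.4 | 0 | 0.8 | 2.0 | 4.0 |

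**Step 5: whether such a change would be noticed as a finding.** Suppose a paired before/after comparison were made in all 321 planned patients with no true difference in ageing. The chance that a two-sided 5% z-test is significant is Φ(b√n/SD − 1.96) + Φ(−b√n/SD − 1.96). For b = 0.5 and SD = 4, b√n/SD = 0.5 × 17.92 / 4 = 2.24, which gives Φ(0.28) = 0.61.

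| b (years) | SD = 4 | SD = 8 |
|---|---|---|
| 0 | 5% | 5% |
| 0.5 | 61% | 20% |
| 1 | 99% | 61% |
| 2 | >99% | 99% |

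A systematic shift does not shrink as patients are added. With zero offset there is no bias and the error rate stays at 5%.

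**The case against.** **Silence in an article.** Cell isolation, array preprocessing and deconvolution are details that an article may leave to the full protocol, a laboratory manual or a SAP, none of which is shown. That stands as a caution: one sentence elsewhere may already settle the matter. It does not remove the point, because the article does not merely omit a step. It states a rule, that timing identifies cell type, and draws an inference from it.

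**The clocks may not depend on the mix.** The Background says that methylation clocks estimate BA accurately in any tissue. That general statement does not show that two leukocyte mixes from one patient give the same reading, and the planned blood-versus-marrow comparison treats compartment as an open question. Still, the documents give no offset, so zero must stay in the range.

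**Stronger readings that the documents do not support.**
- A reader might infer that a composition artefact *will* be reported as ageing. Only *may* is supportable, since the size is unknown.
- A reader might infer that the primary analysis is a formal test of clone minus non-malignant BA. Data analysis specifies no such test; the endpoint is a value for each cell type. The labelling problem remains, but Step 5 is an illustration and not the plan's own test.
- A reader might set the assumed shift against the effect size of 0.5 under Sample size. That figure is a between-patient contrast of BA by frailty. A shift common to all patients at a visit does not bias a comparison between patients at that visit. Only composition differences related to frailty, tolerance or response would do so, and their size is not known.
- A reader might treat the whole change in mix as artefact and want the adjusted value to replace the endpoint. Excess immature cells and basophils at diagnosis are partly the clone itself, so adjustment may remove some of what the endpoint seeks. This objection stands in full and shapes the remedy.

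**Conclusion.** The concern holds in a limited form. Followed as written, the plan cannot separate a treatment-driven change in leukocyte mix from a difference in biological age between the clone and normal cells. Nor can it separate between-patient differences in mix at diagnosis from differences in BA. No covariate named in the article captures composition.

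The size is undetermined: nil if the clocks read leukocyte types alike, and 0.2 to 4.0 years over the non-zero assumed inputs above. The conclusion rests on two premises: bulk blood is what is analysed, and no unseen document provides for sorting or composition adjustment. It affects how the first primary endpoint may be interpreted and, less certainly, the BA–frailty, tolerance and response models. It does not show that any of those analyses is invalid.

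**What to change.** If sorted cells are used, say so and name the fractions; that settles most of the point. Otherwise:

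1. Pre-specify estimation of leukocyte fractions from the same EPIC array at diagnosis, month 3 and month 12.
2. Report a composition-adjusted BA minus chronological age beside the unadjusted value, as a planned sensitivity analysis. Carry both into the BA–frailty, tolerance and response models, including the interim looks at BA and frailty.
3. Check the estimated fractions at diagnosis against the differential count where the CML Observatory or routine care holds one.
4. Attribute a BA difference to the clone or to non-malignant cells only if it persists after adjustment. Failing that, state the limitation.

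**Cost.** No new samples or visits are needed, because the arrays are already planned, though the article does not show that the data exist yet. The work is in the analysis, plus retrieval of differentials where they are held, since Table 2 does not schedule them. The downsides are somewhat wider intervals, uncertain deconvolution in untreated CML blood, and possible over-adjustment at diagnosis. The last is why the adjusted value should accompany the unadjusted endpoint and not replace it.

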#### Secondary objectives

The secondary objectives are:

Describe the distribution of individual clinical frailty levels in a cohort of patients with chronic-phase CML at diagnosis time.Describe tolerance criteria (actual dose received, TKI discontinuation due to intolerance, TKI discontinuation due to adverse events, TKI changes, number of TKI lines and treatment sequences).Evaluate the value of combining BA determination with individual frailty assessment to personalize the management of CML patients treated with TKI, in terms of therapeutic response assessed using the BCR::ABL transcript and quality of life assessed using the EORTC QLQ-C30 questionnaire.

### Participant eligibility

The inclusion and non-inclusion criteria are presented in Table 1. Newly diagnosed chronic phase - CML patients will be eligible for the protocol.

**Table 1 Tab1:** Section criteria

Inclusion criteria	Non-inclusion criteria
Female or male 18 years of age or older	CML in accelerated or blast phase
CML-CP diagnosis (chronic phase) with confirmation of a Philadelphia chromosome (Ph1) made no more than 3 months (90 days) prior to inclusion. A cryptic Ph1 chromosome must be confirmed by FISH. Criteria must meet the CML chronic phase definition criteria: - < 15% blasts in peripheral blood and bone marrow - < 30% blasts + promyelocytes in peripheral blood and bone marrow - < 20% basophils in peripheral blood, - Platelet count ≥ 100 × 109/L (≥ 100,000/mm3)	
BCR ::ABL1 transcript quantifiable by quantitative RT-qPCR	Refusal to participate
1st-line treatment with tyrosine kinase inhibitors	
No treatment with tyrosine kinase inhibitors or hydroxyurea prior to first blood sampling (at diagnosis)	Treatment started before inclusion
Signature of informed consent for the CML Observatory and signature of informed consent for the BIO-TIMER protocol	Patients under guardianship, curatorship, deprivation of liberty or safeguard of justice
Read and understand French	Pregnant or breastfeeding woman
Persons affiliated to a social security system	

